#### Process outcomes

It is important to collect and analyse process outcomes for usual practice and for both testing strategies, as failure to detect differences in early-onset sepsis may be due to poor compliance with the processes, rather than an intrinsic problem with the tests. It will also be important to measure any change in maternal IAP provision and/or neonatal care arising from the strategy allocated. These outcomes will be collected in a consecutive sample of at least 100 women per site, who give birth at gestational age ≥32 weeks (excluding women who have elective caesarean births at rapid test sites). Key parameters that will determine the feasibility and overall effectiveness of the risk factor-based strategy and the two testing groups will include:

Number of women with risk factors for EOGBS infection developing in the baby and which risk factors they have.Number of women having a swab taken (of all those eligible for testing), including site (vaginal-rectal, vaginal only) and person performing the swab (self-swab, healthcare professional).Number of women who decline a swab when offered (and reasons why).Number of women who decline IAP when offered (and reasons why).Number of women having a swab taken at the appropriate time (of all those swabbed and all those eligible).Number of women with a test result available ≥2 hours and ≥4 hours before time of birth.Number of women receiving GBS-specific IAP, antibiotics for prophylaxis before operative (caesarean or instrumental) birth or intrapartum antibiotics for any other reason.Numbers of women with first dose of GBS-specific IAP administered at least 2 hours and at least 4 hours before birth.Total dose of administered IAP per woman.The proportion of women who tested positive for GBS, tested negative for GBS or who did not have an available test result.The proportion of failed tests.Of those who should have been offered IAP according to a positive test result or risk factors, the number of women offered IAP, and the number of women who were not offered IAP.Number of women with a negative test result or no documented risk factors who are offered and accept IAP (and reasons).

Number of babies of mothers who(A) Tested positive for GBS (testing sites).(B) With documented risk factors (risk factor sites) whose vital signs and clinical condition were observed for at least 12 hours who were investigated for infection and/or had intravenous antibiotics commenced.

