## Introduction

 One in four pregnant women in the UK carries group B streptococcus (GBS) in the gut and genital tract. Approximately 50% of babies whose mothers carry GBS will also be colonised, and of those, 3% will develop early-onset GBS (EOGBS) infection.^2^ EOGBS infection (occurring <7 days after birth) is caused by GBS bacteria ascending from the maternal genital tract during pregnancy (usually in the presence of ruptured membranes, although it can occur with intact membranes) or labour.^3^ EOGBS infections tend to manifest as pneumonia and sepsis and affect 1 per 1750 births in the UK (517 babies per year).^4^ GBS is the most common proven cause of early-onset infection (accounting for 40% of all isolates in culture positive cases) in the UK.^3^ One study has estimated that in the UK EOGBS infection causes more than 40 neonatal deaths and around 25 cases of long-term disability every year.^5^ Mortality is around 5%–10%, but higher among preterm babies (23%).^6 7^

Epidemiological studies have suggested that various factors (preterm labour, GBS colonisation or bacteriuria in the current pregnancy, a previous baby with GBS infection, maternal fever during labour) present at the time of birth are associated with the baby having an increased risk of developing GBS infection (presenting as either an early or late onset infection). However, a systematic review estimated that 65% of deliveries had no recognised maternal risk factors for GBS infection.^8^

Giving intrapartum antibiotic prophylaxis (IAP) to mothers who are known to carry GBS has been shown to reduce EOGBS infection.^9^ However, antibiotics may cause short-term complications for the mother (anaphylaxis, medicalisation of labour) or baby (effects on gut microbiome), may have long-term complications for the mother or baby^10^ and may increase antimicrobial resistance both for the individual and the wider population.

The current UK strategy involves identifying maternal risk factors for their baby developing EOGBS infection and then offering these ‘higher risk groups’ IAP.^11^ Additionally, women where GBS detected in a previous pregnancy are offered the option of bacteriological testing in late pregnancy and IAP if GBS-positive, or IAP without testing.

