#### Detailed data collection of testing groups

For determining the process outcomes, individual-level data, not reported in the routine data sources, are required. To collect data on all women would negate the advantages of routine data use, so detailed data collection will be undertaken for a small subset of women at each site.

This will be retrospective source data collection using an online proforma designed for each testing strategy. At each site, individual data for a consecutive sample of at least 100 women per site, at gestational age ≥32 weeks, excluding women admitted for elective caesarean births, will be gathered. This will commence approximately halfway through the site’s data collection period.

This data will be extracted from the women’s healthcare records and transcribed by the research midwife at each site onto the GBS3-specific online database, using the NHS number, postcode and date of birth as the identifiers.

The detailed data collection will provide individual-level data associated with the testing coverage, IAP and resource use for approximately 4000 women in the risk factor-based usual care sites, 2000 women in ECM sites and 2000 women in the rapid testing sites.

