Between-group comparison of the secondary clinical (maternal and neonatal) and process outcomes will also be performed using mixed effect models appropriate for each outcome (linear for continuous outcome and logistic for binary outcomes), adjusting for the minimisation variables and the maternity sites as a random effect and, if applicable, will account for the correlation between outcomes for babies from a multiple pregnancy.

Full details of the planned analyses, including sensitivity and secondary analyses of the primary outcome, secondary outcomes and process outcomes, will be documented in the Statistical Analysis Plan prior to any analysis and made publicly available on the trial registry (ISRCTN49639731).

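### The process-outcome sample has two conflicting elective-caesarean exclusions, and one neonatal process outcome uses a different denominator in each group, so some planned between-group process comparisons would not compare like with like

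*Protocol article*

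**What the plan says.** Two sections of the protocol article define the sample for the process outcomes. Both ask for at least 100 consecutive women per site from 32 weeks' gestation.

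- *Process outcomes* limits the caesarean exclusion to one type of site: "excluding women who have elective caesarean births at rapid test sites".
- *Detailed data collection of testing groups* sets no such limit. At each site it takes a "consecutive sample of at least 100 women per site, at gestational age ≥32 weeks, excluding women admitted for elective caesarean births".

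The second section is the data source for the first: "For determining the process outcomes, individual-level data, not reported in the routine data sources, are required". Its heading mentions only testing groups, but its text also counts the control group: "approximately 4000 women in the risk factor-based usual care sites, 2000 women in ECM sites and 2000 women in the rapid testing sites".

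The last item under *Process outcomes* counts babies who were observed, investigated for infection or started on intravenous antibiotics. At testing sites these are babies of mothers who tested positive. At the other sites they are babies of mothers "With documented risk factors (risk factor sites) whose vital signs and clinical condition were observed for at least 12 hours".

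*Statistical analysis* then states: "Between-group comparison of the secondary clinical (maternal and neonatal) and process outcomes will also be performed using mixed effect models". The adjustment is for the minimisation variables, with site as a random effect.

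**The concern.** If elective caesareans are left out at rapid sites and kept elsewhere, the ECM and risk-factor samples contain women who have little occasion for prophylaxis in labour, and the rapid sample does not. A difference in prophylaxis or swab uptake could then come from the sampling rule alone.

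The neonatal item has a different fault, which remains whichever sampling rule applies. Testing positive and having a risk factor are different conditions. Both are established after the site was randomised, and the first depends on the strategy itself. A comparison of proportions within these subsets is not a randomised comparison.

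The process data have real work to do. The article wants them to show whether a null primary result reflects poor compliance, and to measure how the strategies change prophylaxis and neonatal care. *Objectives* makes sample provision an ECM-versus-rapid question, and *Economic evaluation* takes test and prophylaxis uptake from the same records.

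**Working it through.** **The plan's own sample figure.** 100 women × 80 sites (the maximum in the abstract) = 8000. Split 1/2, 1/4, 1/4, this gives 4000 / 2000 / 2000, as stated. The 71 listed sites would give 7100, or 3550 / 1775 / 1775, as a minimum. The stated counts therefore cover all three groups, so the exclusion in that section applies to risk-factor sites as well and does conflict with the one under *Process outcomes*.

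**Effect of the rapid-site-only rule on prophylaxis.** Let *c* be the elective share of sampled births where such births are kept. The article does not give it, so 5–20% is assumed. Let *r* be the rate of GBS-specific prophylaxis in all other births, equal in every group. Assume a rate near zero at elective caesarean.

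- Rapid sites show *r*; ECM and risk-factor sites show *r*(1 − *c*). Ratio = 1/(1 − *c*); difference = *rc*.
- Pooled testing, with ECM and rapid weighted equally, shows *r*(2 − *c*)/2. Ratio to risk factor = (2 − *c*)/[2(1 − *c*)]; difference = *rc*/2.

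| *c* | Rapid vs ECM or risk factor | Difference at *r* = 30% | Pooled testing vs risk factor | Difference at *r* = 30% |
|---|---|---|---|---|
| 5% | 1.05 | 1.5 points | 1.03 | 0.75 points |
| 10% | 1.11 | 3.0 points | 1.06 | 1.5 points |
| 15% | 1.18 | 4.5 points | 1.09 | 2.25 points |
| 20% | 1.25 | 6.0 points | 1.13 | 3.0 points |

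The 30% is also an assumption; the ratios do not depend on it. If the every-site rule governs, each ratio is 1.00.

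**Swab uptake, ECM versus rapid.** ECM eligibility includes women with a planned elective caesarean; rapid testing excludes them. Assume 80% uptake in all other women under both tests, *c* = 10–20%, and uptake *e* of 30–80% in elective caesareans at ECM sites. ECM uptake is 0.80(1 − *c*) + *ec*. The lowest value is 0.80 × 0.80 + 0.30 × 0.20 = 70%, and the highest is 80%, against 80% for rapid.

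**Neonatal denominators.** As illustrative subset sizes, take the *Introduction*'s carriage of one in four (25%) and, from its statement that "65% of deliveries had no recognised maternal risk factors for GBS infection", 100% − 65% = 35% with a risk factor. Suppose each group's count under this item is 50 babies per 1000 births:

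- testing sites: 50/250 = 20.0%
- risk-factor sites: 50/350 = 14.3%
- ratio = 350/250 = 1.40, from the denominators alone.

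The article's own rules show the mismatch without any assumed figure. The sample starts at 32 weeks, routine rapid testing starts at 37 weeks, and preterm labour is both an exclusion from testing and a listed risk factor. Babies born after preterm labour at 32–36 weeks therefore count at risk-factor sites and in general do not count at rapid sites. Women without a timely result are managed on risk factors, and their babies also fall outside the test-positive denominator.

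**The case against.** The strongest reply has four parts.

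1. **The caesarean artefact is conditional.** It arises only if the *Process outcomes* wording governs, and the full protocol is not shown. This is right. What is established is a conflict between two statements of one rule; the bias follows under one of them.

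2. **The sentence on between-group comparison is generic.** It refers to models appropriate for each outcome and leaves details to the analysis plan. It cannot mean that every item is compared across all groups, because failed tests, for example, have no counterpart where no routine testing is done. This is fair: a direct model of the two neonatal subsets is a natural reading, not a stated intention. But the article fixes group-specific denominators and announces between-group comparisons without separating the two.

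3. **Conditional denominators suit adherence.** Offer of prophylaxis among women with an indication is properly measured in those women. This stands for description within a group.

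4. **Unconditional measures already exist.** Prophylaxis receipt, timing of the first dose and total dose are listed without a test or risk-factor condition, and neonatal specialist admission is a secondary outcome. This stands. A reader might infer that all the prophylaxis comparisons use group-specific denominators; the text does not support that.

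A reader might also assume that 80% of babies in each subset are observed and conclude that the true burden is 0.25 × 0.80 = 20% of births under testing against 0.35 × 0.80 = 28% under risk factors. The documents do not support this. Testing sites also act on risk factors, so the 20% omits babies of risk-factor mothers who were untested or tested negative, and it assumes that every woman is tested.

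**Conclusion.** The concern holds in two limited parts.

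First, the article gives two incompatible elective-caesarean exclusions for one sample. Under the rapid-site-only rule, and only then, prophylaxis use would be inflated at rapid sites by a factor of 1.05–1.25, or 1.03–1.13 on the randomised contrast of testing against risk factor. These ranges rest on an assumed elective share of 5–20% and near-zero GBS-specific prophylaxis at elective caesarean; a higher rate there would shrink them.

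Second, the item on neonatal observation, investigation and antibiotics cannot serve as a between-group comparison as defined. The factor of 1.40 illustrates how far denominators alone can move it and is not an estimate of bias in this trial.

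Neither part touches the primary outcome, its analysis or the sample size. It should be corrected before the process outcomes are analysed, but it is not critical to the trial's main conclusion.

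**What to change.** - State one rule for the process-outcome sample and use it in both sections, with one definition of an elective caesarean (the two sections differ between having one and being admitted for one).
- In every between-group process comparison, apply the same elective-caesarean exclusion to all three groups. Report ECM-site elective caesareans separately, with their test uptake, so that the ECM strategy is fully described and the economic inputs stay complete.
- Report outcomes conditional on a positive test or on risk factors (the neonatal item, and prophylaxis offered among women with an indication) as adherence within each group only.
- Compare prophylaxis receipt with all sampled women as the denominator. Compare neonatal observation, investigation and antibiotics with all sampled babies as the denominator, where these were recorded for all of them.

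**Cost.** Mostly wording and a filter on mode of birth. If elective caesareans were collected at ECM and risk-factor sites, those groups lose that share of women from the comparisons (5–20% on the range assumed here). Data collection ended on 31 March 2024, so if the data form recorded neonatal care only for babies of test-positive or risk-factor mothers, the all-babies contrast may be limited or impossible, and the report should say so.

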#### Additional descriptors

Descriptors of the dataset population as listed below will be collected and compared:

Maternal age at booking.Parity at booking.Ethnicity.Smoking at booking.Index of Multiple Deprivation for maternal home at the time of childbirth.Number of fetuses (seen at dating ultrasound scan).Birth order.Baby’s sex.

The occurrence of an adverse event as a result of participation within this trial is not expected, and no adverse event data will be collected.

#### Trial phases

Testing sites have training and site-set up meetings with members of the trial team, including on-site training on the GeneXpert system if applicable. The testing strategies were implemented at sites for a period of up to 12 weeks before the start of the data collection phase.

During the 12 week implementation period, the number of tests performed as a percentage of those eligible for testing (from the site’s reported birth records) is monitored by the GBS3 coordinating centre. The target is at least 80% coverage (If actual birth rates are unavailable, estimation is based on previous years’ birth rate at site). Cascaded training by site staff trained on GBS3 during this implementation period should ensure all midwifery teams and midwives covering different shifts are trained promptly and appropriately. If the 80% testing coverage is met before 12 weeks, the site starts the study data collection period.

Sites will not be withdrawn if they fail to achieve the 80% test uptake rate by 12 weeks. At 12 weeks, the site will open to data collection regardless of testing coverage, and its data will be included in the primary analysis.

The first testing site entered the data collection period on 28 December 2021.

#### Detailed data collection of testing groups

For determining the process outcomes, individual-level data, not reported in the routine data sources, are required. To collect data on all women would negate the advantages of routine data use, so detailed data collection will be undertaken for a small subset of women at each site.

This will be retrospective source data collection using an online proforma designed for each testing strategy. At each site, individual data for a consecutive sample of at least 100 women per site, at gestational age ≥32 weeks, excluding women admitted for elective caesarean births, will be gathered. This will commence approximately halfway through the site’s data collection period.

This data will be extracted from the women’s healthcare records and transcribed by the research midwife at each site onto the GBS3-specific online database, using the NHS number, postcode and date of birth as the identifiers.

The detailed data collection will provide individual-level data associated with the testing coverage, IAP and resource use for approximately 4000 women in the risk factor-based usual care sites, 2000 women in ECM sites and 2000 women in the rapid testing sites.

#### End of data collection period

The GBS3 coordinating centre will inform the site that the standard data collection period at the site has ended and the site will revert back to the strategy undertaken prior to involvement in the GBS3 trial (eg, risk factor-based strategy). The site will be closed after completing all necessary close-out procedures, coordinated by the GBS3 coordinating centre.

The last site completed data collection on 31 March 2024.

### Routine data sources

Data sharing agreements between the sponsor and data provider will enable the University of Nottingham to receive routine data for the GBS3 Trial from various sources (table 1). Routine data and the detailed dataset will be safely stored in an accredited Trusted Research Environment (Data flow charts online supplemental appendices 4A–C).

**Table 1 T1:** Routine data sources for GBS3 Trial

Data source	Description and use for GBS-3 trial
English Maternity Services Dataset (MSDS version 2) Maternity Services Data Set (MSDS) - NHS Digital and NHS Wales Informatics Service	These are patient-level datasets that capture key information at each stage of the maternity care pathway including the mother’s demographics, booking appointments, admissions and readmissions, screening tests, labour and delivery along with the baby’s demographics, admissions, diagnoses and screening tests. These will provide maternal secondary outcomes and other descriptive details.
UK Health Security Agency UK Health Security Agency - GOV.UK (www.gov.uk), Health Protection Wales Health Protection - Public Health Wales (nhs.wales)	Confirmed cases of all-cause early and late-onset neonatal sepsis and maternal sepsis identified through positive culture of a pathogenic bacteria.
National Neonatal Research Database Neonatal Data Analysis Unit | Faculty of Medicine | Imperial College London	Information on clinically suspected (negative or unknown culture status with ≥3 agreed clinical signs/symptoms, treated with antibiotics ≥5 days, within 7 days of birth) all-cause early neonatal sepsis, other secondary neonatal outcomes. All participating sites contribute data to this dataset.
Badgernet (Maternity)	Available as either a brief clinical summary record or a complete electronic health record system that captures all aspects of care and outcomes from booking to discharge from postnatal care. The latter system is used by more than 25% of English units. Data from the system would enable babies not ill enough to be admitted to a neonatal unit, and who remain on the postnatal ward, to be added to the trial dataset.
Badgernet (Neonatal)	This is the main source of the NNRD, along with additional variables which can add richer data for the primary outcome adjudication
Paediatric Intensive Care Audit Network Database	An audit database recording individual details of the diagnosis and treatment of all critically ill babies in paediatric intensive care units. This will identify newborns not admitted to the neonatal unit or discharged and later readmitted to hospital (within 7 days of birth) with sepsis
Hospital Episode Statistics (England) and NHS Wales Informatics Service.	These contain details of all admissions, outpatient appointments and accident and emergency attendances at NHS hospitals in England and Wales, respectively.
Office for National Statistics	This will capture neonatal deaths and maternal deaths that happen at home and were not reported to a hospital.

GBS, group B streptococcus; NHS, National Health Service.

### Sample size and justification

The sample size is based on the rate of all-cause early-onset neonatal sepsis between the routine testing and the risk factor-based randomised strategies. The NSC model^23^ estimated a rate of culture positive EOGBS as 0.49/1000 live births with the risk factor strategy. Assuming GBS contributes 50% of all early-onset neonatal infection,^24^ then the all-cause rate would be 0.98/1000 live births. The trial was designed to detect a 40% reduction in all-cause early-onset neonatal sepsis based on assuming that IAP would have an effect on 73% of early-onset neonatal infections caused by GBS and other Gram-positive infections, with no impact on the other 27% of cases caused by *Escherichia coli* and other Gram-negative infections and an effect of IAP on Gram-positive infections of 0.44, consistent with a Cochrane review^9^ and in line with the trends seen in the USA following introduction of testing.

To detect a 40% reduction (a reduction in event rate from 0.000986 to 0.0005916), with a 90% power and two-sided significance level of 5%, a total sample size of 2 12 960 women would be required without inflation for clustering effect. This infection rate estimate is conservative as it is based on culture-confirmed cases only, so the inclusion of clinically suspected cases will likely increase the power. There are no published estimates for the hospital-level intracluster correlation coefficient (ICC) for early-onset neonatal infection, but we would expect any variations in the infection rates across clusters to be a result of individuals’ clinical or demographic risk factors, biochemical or molecular markers, or bacterial load rather than hospital-level factors, hence we chose a small ICC of 0.0001. Assuming this ICC, an average cluster size of 4500 (calculated using published NHS Maternity statistics for deliveries in consultant-led or AMUs with a minimum of 3000 deliveries per annum) and allowing for a coefficient of variation in cluster size of 0.31 (CV), the design effect for the sample size would be around 1.5, calculated from the formula: Design effect=1+[(1+CV^2^) $\overset{-}{m}$−1]ρ where CV is the coefficient of variation, $\overset{-}{m}$ is the average cluster size, and ρ the ICC.

Adjusting for the design effect would lead to a total sample size of 320 000 women. These could be recruited from a minimum of 72 maternity sites.

During the course of the trial to date, we have reviewed the design effect parameters which were initially specified, to check any changes with time. We noticed that the average cluster size had reduced due to a reduction in birth rates since the original protocol and an increase in the NHS national data opt-out for use of data for research purposes in women of childbearing age in England. As a result, we opted to relax the requirement of a minimum of 3000 deliveries per year to 2000 deliveries per year (implemented 6 September 2022) to increase the pool of potential sites and, in addition, to allow variable data collection periods for each site from 9 to 16 months, rather than fixed at 12 months. Based on the number of births per year for participating sites, the projected length of the data collection period was determined such that by combining information on the average cluster size and CV, the effective sample size of 212 960 women would be maintained. This resulted in assuming an average cluster size of 4750 with a CV of 0.46.

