**Sites and participants:**

320 000 women from up to 80 hospital maternity units.

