**Trial registration number:**

ISRCTN49639731.

STRENGTHS AND LIMITATIONS OF THIS STUDYThis study is a cluster randomised trial to determine the clinical and cost effectiveness of routine testing for group B streptococcus in pregnancy.320 000 participants will be adequately powered to detect a small but meaningful difference in early-onset neonatal sepsis.The study is not designed to detect a difference in early-onset neonatal sepsis between the two testing strategies but will provide information on acceptability and ease of implementation of the two testing strategies.

We use the term ‘women’ throughout to refer to those who are pregnant and give birth. We acknowledge that not all people who are pregnant and give birth identify as women, and it is important that evidence-based care for maternity, perinatal and postnatal health is inclusive.^1^

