## Methods and analysis

### Setting and site level eligibility

Maternity hospitals (obstetric units (OU) and alongside midwifery units (AMUs)) if able to accept women requiring IAP are eligible to participate if, with training and support, they are able to implement the antenatal ECM or intrapartum rapid testing strategies. A list of 67 participating hospital trusts and health boards making up 71 sites in England and Wales is provided in online supplemental file 1.

One National Health Service (NHS) Trust may contain several maternity units. Each unit is then considered as an individual cluster site if the routine data sources could discriminate between the maternity units within the Trust and each maternity unit was able to maintain its allocated group.

The contracted microbiology laboratories providing services to the sites had to be prepared to use Public Health England (PHE, now UK Health Security Agency) Standard for Microbiological Investigations (SMI) B58 for the ECM testing for GBS for the duration of the trial. The PHE SMI B58 is the national guidance on the UK Standards for Microbiology Investigations for detection of carriage of GBS.^17^ Participating sites also had to be prepared to host a Cepheid GeneXpert system in a location convenient to the delivery suite.

Randomisation is at the site level to avoid any risk of contamination. Eligible sites are randomised on a 1:1 ratio to a routine testing strategy or to the risk factor-based strategy, using a minimisation algorithm with a random element.

Minimisation variables were overall number of births per year (<4000, 4000–4999 and ≥5000), according to national data for preceding year; neonatal unit level of care tier associated with the participating maternity unit (special care unit, local neonatal unit or neonatal intensive care unit)^18^ and presence of AMU.

There was a further second-level randomisation of the routine testing sites to either antepartum ECM testing or intrapartum rapid testing, restricted to achieve balance.

Withdrawal of sites after randomisation is avoided, if at all possible, in order to reduce bias.

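### The headline total of 320,000 women is out of date: the revised cluster size and CV need about 335,500 to keep the effective size that the plan says it maintains

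*Protocol article*

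**What the plan says.** All places are in the protocol article.

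- **Sample size and justification, original calculation.** The target difference is "a reduction in event rate from 0.000986 to 0.0005916", "with a 90% power and two-sided significance level of 5" per cent. This leads to "a total sample size of 2 12 960 women would be required without inflation for clustering effect". With an ICC of 0.0001, an average cluster size of 4500 and a CV of 0.31, the design effect is put at around 1.5. The section continues: "Adjusting for the design effect would lead to a total sample size of" 320,000, from at least 72 sites.
- **Same section, revision.** Birth rates fell and data opt-outs rose. The minimum site size was therefore lowered, and collection periods were allowed to run from 9 to 16 months, with lengths projected so that the effective size of 212,960 would be kept. "This resulted in assuming an average cluster size of 4750 with a CV of 0.46". No revised design effect or total follows.
- **Setting and site level eligibility.** There are 71 participating sites. "Eligible sites are randomised on a 1:1 ratio to a routine testing strategy or to the risk factor-based strategy".
- **Abstract, Sites and participants.** The trial size is 320,000 "women from up to 80 hospital maternity units".
- **Strengths and limitations box.** 320,000 participants "will be adequately powered to detect a small but meaningful difference in early-onset neonatal sepsis".

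**The concern.** A larger average cluster and a larger CV both raise the design effect. If the effective size is held at 212,960, the total has to rise. The article changes both inputs, says the effective size is unchanged, and still carries the old total in its two most visible places. These are current statements, not a record of superseded text: the same article reports that the last site finished data collection on 31 March 2024, well after the revision.

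What is at stake is how the trial is read. Readers will compare the number analysed with the stated size. If about 337,000 women are analysed, it will look like unexplained over-recruitment. If about 320,000 are analysed, it will look as though the target was met, although the effective size said to be maintained was missed.

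**Working it through.** **Inputs.** Event rates 0.000986 and 0.0005916, 90% power, two-sided 5%, ICC 0.0001, original m = 4500 and CV = 0.31, revised m = 4750 and CV = 0.46, all from the sample size section. The 1:1 allocation and the 71 sites come from the setting section.

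**1. Reproduce the unclustered size.** For two proportions with pooled variance under the null and no continuity correction:

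n per arm = [1.96 × √(2p̄(1 − p̄)) + 1.2816 × √(p1(1 − p1) + p2(1 − p2))]² / (p1 − p2)²

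where p̄ = 0.0007888. This gives 106,481 per arm and 212,962 in total, against 212,960 stated. It agrees.

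**2. Reproduce the original total.** The article's formula is DE = 1 + [(1 + CV²) × m − 1] × ICC.

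- DE = 1 + [(1 + 0.0961) × 4500 − 1] × 0.0001 = 1 + 4931.45 × 0.0001 = 1.4931
- 212,960 × 1.4931 = 317,980, or 212,960 × 1.5 = 319,440 with the rounded value
- 320,000 / 4500 = 71.1, hence 72 sites

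So 320,000 and 72 sites follow correctly from the original inputs.

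**3. Apply the same formula to the revised inputs.**

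- DE = 1 + [(1 + 0.2116) × 4750 − 1] × 0.0001 = 1 + 5754.1 × 0.0001 = 1.5754
- Required total = 212,960 × 1.5754 = 335,499
- 335,499 / 320,000 = 1.048, so about 15,500 women or 4.8% above the headline
- 335,499 / 4750 = 70.6, hence 71 sites, which is the number listed

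**4. Effective size and power for each total.** Effective size is the total divided by DE. Power is from the normal approximation matching step 1, with half the effective size per arm.

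| Scenario | Total women | DE | Effective size | Power |
|---|---|---|---|---|
| 71 sites × 4750 | 337,250 | 1.5754 | 214,071 | 90.1% |
| 320,000 at an average of 4750 | 320,000 | 1.5754 | 203,122 | 88.6% |
| 320,000 over 71 sites (average 4507) | 320,000 | 1.5460 | 206,989 | 89.2% |

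All rows use CV = 0.46. For the last row, DE = 1 + [1.2116 × 4507 − 1] × 0.0001 = 1.5460. Against 212,960, the second row is short by 9,838 effective women (4.6%) and the third by 5,971 (2.8%). On neither reading do 320,000 women deliver the maintained effective size.

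**The case against.** **The design is not underpowered.** A reader might infer from the gap that the trial has lost its 90% power. The article does not support that. The revision fixes the effective size, not 320,000, and 71 sites at an average of 4750 exceed what is required. This stands in full.

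**Nothing stops at 320,000.** A reader might also infer that data extraction could be closed at that count. No such rule appears. The dataset is defined by births within each site's study period, apart from stated exclusions and opt-outs. The coordinating centre ends each site's period, its length was projected from the effective size, and collection has finished. This stands too.

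**The original derivation is correct.** It reproduces from the inputs printed beside it. Putting 335,500 there would create an arithmetic error that is not there now. This limits where the correction belongs.

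**The gap is small and the ICC is a guess.** The article says there are no published estimates. With the revised m and CV, 320,000 women would meet 212,960 at an ICC of (320,000/212,960 − 1)/5754.1 ≈ 0.000087 instead of 0.0001. The strengths box gives no power percentage, and the event rate is described as conservative because it counts only culture-confirmed cases. All this is fair and keeps the point modest. It does not reconcile the two totals: a higher ICC would widen the gap, the gain from clinically suspected cases is not quantified, and the article's own assumptions still give 335,500.

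**Conclusion.** The point holds as a stale sample size figure. The 320,000 in the abstract and strengths box belongs to the original cluster size and CV. Under the revised inputs and the article's own formula, the matching total is about 335,500, which is 4.8% higher. The statement that the effective size is maintained agrees with the revised inputs and the 71 listed sites; it does not agree with 320,000.

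The 90.1% figure for the revised design assumes that all 71 sites contribute, that 4750 is the average number of women per site after opt-outs over its actual collection period, and that the ICC is 0.0001. If only 67 clusters contributed at that average (318,250 women), the effective size would be 202,011 and power 88.4%.

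**What to change.** 1. In the sample size section, directly after the revised cluster size and CV, state the revised design effect (1.58), the required total (about 335,500 women) and the projected total (about 337,000 from 71 sites).
2. Align the 320,000 in the abstract and the strengths box with that statement.
3. Leave the derivation of 320,000 from 4500 and 0.31 as it is, and label it as the original calculation.
4. If the final dataset holds only about 320,000 women, report power of about 88.6–89.2% under the planning assumptions in place of 90%.

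The cost is a few sentences. No extra recruitment or change to the analysis is needed.
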